#### Missing data

After maximal efforts have been employed to minimise the presence of missing data, we will employ, beyond the default complete case analysis, a multiple imputation approach to assess the robustness of results.^44^

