Reasons for discontinuation are the following: (1) withdrawal of informed consent, (2) participants from the CG (without EME) starting in an OT-EME group during the data collection phase and (3) participants of the EG (with EME) missing more than three of the eight EME lessons. All data collected until withdrawal will be used in the analysis. If a participant decides to withdraw from the follow-up, the reasons for the withdrawal will be recorded for the subsequent analysis respectively the interpretation of the results. We will make all attempts to closely follow up participants and therefore minimise missingness throughout data collection. At each time point, participants of both groups will be invited to fill in the questionnaires via Redcap by presenting or e-mailing the correct web link and, if necessary, up to two reminders after 4–5 days each. No reaction will lead to a reminder for contacting the principal investigator, if they need any support to continue with the study, with a clear statement, that they are not obliged to answer this reminder or justify their drop-out if they do not want to.

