### Statistical methods and analysis

#### Sample size

The target study population are people with post-COVID-19 condition living in Switzerland. To calculate the sample size of this study, we used data from two previous studies. In the feasibility study with persons with long COVID-related fatigue, the mean difference of the primary outcome (self-efficacy in performing energy conservation strategies) at T2 (post-intervention) was 1.9 (95% CI: 2.89 to 0.90).^23^ We hypothesised, therefore, a difference of 1.5 points at T2 and conservative assumption of a SD of 2.2 points.^38^ Including a follow-up rate of 24% at T2, the estimated sample size to detect a difference of 1.5 points with 90% power (0.05 alpha) is 122 persons. Therefore, we aim at a total of 122 persons included in the study (eg, 61 and CG: 61).

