Cost-effectiveness of EME intervention against the standard care only will be evaluated by performing an economic evaluation, using the direct costs of delivering the intervention, disease-related and productivity as the cost input and various outcomes as health effects. A probabilistic sensitivity analysis will be performed to consider the uncertainty in the various input parameters and their effects on the decision-making process. After the maximal efforts have been employed to minimise the presence missing data, we will employ, beyond the default complete case analysis, a multiple imputation approach to assess the robustness of results.^44^ Statistical analysis will be performed using Stata (Stata, College Station, Texas, USA) and R (R Core Team (2023) R: A Language and Environment for Statistical Computing. R Foundation for Statistical Computing, Vienna, Austria; <https://www.R-project.org/>).

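### The default complete-case analysis does not fit the promise to use all data up to withdrawal or the repeated-measures mixed model, and it risks a modest bias at T2

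*Protocol article*

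**What the plan says.** Four statements in the protocol article bear on this.

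- **Missing data:** "we will employ, beyond the default complete case analysis, a multiple imputation approach to assess the robustness of results".
- **Statistical analysis:** the same rule appears at the end of the paragraph on the economic evaluation, "beyond the default complete case analysis, a multiple imputation approach to assess the robustness of results". Because it also stands alone under Missing data, it cannot be read as applying to costs only.
- **Data collection**, after the reasons for discontinuation: "All data collected until withdrawal will be used in the analysis".
- **Statistical analysis:** an adjusted repeated-measures mixed-effects linear model is named for all continuous primary and secondary outcomes, with the per-protocol effect as the causal contrast.

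Outcomes are measured at T0, T1 (week 6), T2 (week 14, the main assessment) and T3 (week 24). The Sample size section counts on "a difference of 1.5 points at T2 and conservative assumption of a SD of 2.2 points" and allows for attrition with the phrase "Including a follow-up rate of 24% at T2".

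**The concern.** A complete-case set, as the term is normally used, contains only participants with no missing value among the variables analysed. Someone who answers at T0 and T1 and then leaves contributes nothing, although the Data collection section says those answers will be used. Both rules cannot govern the primary result, and two analysts following the text could analyse different sets of people.

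The choice matters because T1 falls after lesson 7 and is the last observation before the main assessment. If people who leave differ at T1 from those who stay, and differ in another way in the other group, the completers' T2 contrast is distorted. A likelihood-based mixed model keeps the T1 information and is valid when dropout depends on observed scores (missing at random). Complete case needs a more restrictive assumption. Outcome-related dropout that differs by group is plausible: the experimental group is discontinued for missing more than three of eight lessons, the control group for starting an EME group, and the two are recruited differently (clinic patients against self-registered volunteers).

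**Working it through.** **1. The plan's own figure.** Inputs from the Sample size section: difference 1.5, SD 2.2, 90% power, alpha 0.05 (taken as two-sided), 24% at T2.

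n per arm = 2 × (1.960 + 1.282)² × 2.2² / 1.5² = 2 × 10.51 × 4.84 / 2.25 = 45.2, so 46.
Inflated: 46 / 0.76 = 60.5, so 61 per arm and 122 in total.

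This matches the protocol exactly. The 24% is printed as a follow-up rate, but only loss reproduces 122: if 24% were retained, 46 / 0.24 gives 192 per arm, or 384. The 24% is therefore used below as loss.

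**2. Power of a complete-case comparison at T2.** Expected with T2 observed: 61 × 0.76 = 46.4 per arm.

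z = 1.5 / (2.2 × √(2 / 46.36)) − 1.960 = 3.283 − 1.960 = 1.323, so power is 90.7%.

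If complete case instead required all four visits, with an assumed further share missing T3 or another visit:

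| Further missing (assumed) | Per arm | Power |
|---|---|---|
| 5% | 44.0 | 89.2% |
| 10% | 41.7 | 87.6% |
| 20% | 37.1 | 83.6% |

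**3. Bias and precision by simulation.** From the protocol: 61 per arm, SD 2.2, T2 effect 1.5, 24% loss. Assumed, because the protocol gives no figures: loss occurs between T1 and T2, equal correlation between visits of 0.5, 0.6 or 0.7, T1 effect 1.0, and the log-odds of dropout per SD of T1 shown below. Two analyses are compared: (a) complete-case regression of T2 on group and T0; (b) a likelihood estimate that keeps the T0 and T1 data of those lost, combining T2 given T0, T1 and group (completers) with T1 given T0 and group (everyone). Bias was taken from very large simulated samples.

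| Dropout depends on T1 | Bias of (a), points | Share of 1.5 |
|---|---|---|
| Not at all | about 0 | 0% |
| Equally in both groups | about 0 | 0% |
| Experimental group only, low scorers leave, log-odds 1.0 to 1.5 | +0.10 to +0.16 | 7 to 11% |
| Control group only, low scorers leave, log-odds 1.0 | −0.10 to −0.12 | 7 to 8% |
| Opposite directions, log-odds 0.7 each | +0.15 to +0.17 | 10 to 11% |
| Opposite directions, log-odds 1.0 to 1.5 each | +0.20 to +0.31 | 13 to 21% |

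The likelihood estimate (b) was about unbiased in these scenarios (within about 0.01 points).

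Standard error at T2 when dropout is unrelated to T1:

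| Correlation | (a) | (b) |
|---|---|---|
| 0.5 | 0.406 | 0.400 |
| 0.6 | 0.363 | 0.357 |
| 0.7 | 0.328 | 0.322 |

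Over the scenarios in which standard errors were compared, keeping the T0 and T1 data lowered the variance by 0 to 5%.

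**The case against.** The best defence is that the article never defines the term. In a mixed model with one row per visit, complete case can mean that only rows with a missing value drop out while the person's other visits stay. On that reading the statements agree. It is possible, but it is not stated, it is not the usual meaning, and setting imputation beside a default complete-case analysis suggests deletion of people. Multiple imputation is indeed planned, but only to assess robustness, so it does not produce the headline estimate.

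Several stronger inferences are tempting, and the protocol does not support them.

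- **That the T2 effect will be biased.** No dropout pattern is given, and nothing shows that dropout follows T1 self-efficacy. Bias is nil if loss is completely random, depends only on model covariates, or acts equally in both groups. It also vanishes if the estimate is change from T0 and the T1–T2 correlation equals the T0–T1 correlation, since the change is then uncorrelated with T1.
- **That the bias reaches a fifth or more of the target when only experimental-group dropout depends on T1.** An unadjusted completers' difference gives 0.22 to 0.42 points in that scenario, but the plan specifies an adjusted model. Baseline self-efficacy is not named among the covariates, so adjustment for it is itself an assumption, but T0 is measured in both groups and the adjusted figures are the fairer guide.
- **That the trial loses power.** The 122 already allows for the 24% loss. A shortfall arises only if a missing T3 also removes a T2 value, which the protocol does not say.
- **That questionnaire follow-up differs by group.** The Data collection section gives both groups the same REDCap invitations and reminders. Only the discontinuation rules and recruitment routes differ.

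**Conclusion.** The inconsistency stands. The article twice fixes complete case as the default, and in its ordinary sense that conflicts with using all data up to withdrawal and wastes the planned mixed model's ability to use incomplete follow-up. The consequence is conditional and modest: about 0.10 to 0.16 points in the baseline-adjusted T2 self-efficacy effect if dropout depends on T1 in the experimental group only, up to about 0.3 if strong dependence runs in opposite directions, and none if the groups behave alike. These sizes rest on the assumed correlations, T1 effect and dropout strengths, and on reading 24% as loss. Loss of precision is a minor point. The reason to act is that the better analysis is already named in the plan.

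**What to change.** In the Missing data section and its repeat under Statistical analysis, replace the complete-case default with one rule. The primary analysis is the likelihood-based mixed model already named, fitted to all observed outcomes. For the per-protocol contrast this means all data up to withdrawal or discontinuation, in line with the Data collection section. Use multiple imputation for missing covariates and costs and as a robustness check, and keep complete case as a sensitivity analysis, stating which missing visits exclude a participant. A delta-shift analysis for data not missing at random is optional.

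The cost is wording and minor programming, with no new data and no change to the 122. Analysis is scheduled to begin at the end of 2025 after the last T3 assessment, so the rule can be settled before outcomes are analysed.

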#### Volunteer bias

The fact that only persons who have actively registered themselves in the register can potentially get part of the CG will be carefully considered when interpreting and discussing the results of this study.

#### Selection bias

This common flaw of observational studies, we address by not using any information collected in the EG after the baseline period to determine which individuals from the register should be enrolled in the CG. By defining the recruitment of controls in two stages and having clear eligibility criteria, we create a structured approach to estimate causal effects even in the absence of true randomisation, based on an unbiased sample.

### Ethics and dissemination

Fatigue is a common and disabling condition for people with long COVID. The self-management education of persons enables them to implement new behavioural habits and engage more successfully in daily routines and social participation by managing their available energy. In the field of rehabilitation, this research will deliver urgently needed data on the effectiveness of an intervention recommended by guidelines for persons with long COVID and give a perspective on the potential and meaning of self-management education concerning health and well-being. Furthermore, the register of persons with a clinical history of long COVID can be used for further observational and evaluation studies, especially considering a long-term perspective. In the actual healthcare context in Switzerland, several factors prevent conducting an RCT or quasi-RCT aiming at investigating the effectiveness of EME in persons with long COVID-related fatigue: (1) in those institutions where the EME protocol with peer groups has been implemented as part of the standard care, it would not be feasible and/or ethical to introduce an alternative OT intervention acting as a CG intervention. (2) Enough patients must enter an OT service to continuously form and maintain EME groups. Randomisation into two groups would reduce the possibility of forming groups and prevent EME from being performed. (3) Furthermore, randomisation into a waiting list is not feasible because, in the case of EME, this would require at least 15 weeks, which would be an unnecessary additional patient burden.

Regarding OT, this research project will support the further development of evidence-based practice and use of standardised treatment protocols, which are until to date lowly applied in the daily practice of OTs in Switzerland.^45^ Data from the survey on the implemented energy management strategies will inform OTs about the most effective as well as the most difficult strategies to implement and provide insights into predicting factors and successful behavioural changes. This kind of knowledge in OT was, until now, missing or is, at present, only subjectively and empirically. Furthermore, OT researchers are asked to contribute their perspective to the development and discussion of the science of habit because a better understanding of the factors that support changes in habits and routines is also relevant in other health areas (eg, pain management, ergonomic behavior, stress management and lifestyle behaviour).^46^ The findings of this study will support the training of OTs in general and especially those delivering self-management education and support their skills in coaching and empowering patients and offering a more informed perspective for persons with long COVID.

This study will answer whether a higher effect justifies the effort of organising groups or if individual OTs are sufficiently empowering. At the same time, data from the cost-effective analysis will support rehabilitation managers, assurances and policymakers with data for informed decisions about group-based rehabilitation interventions.

The results of this study will be published as articles in scientific journals from various fields and presented at national and international congresses. In addition, we will disseminate the results through the social media channels of the partner organisations (Altea Network and Long-COVID-Switzerland), media dedicated to practitioners (OT and medical staff) and general media. In the training courses for EME-leading OTs and workshops for other healthcare professionals (eg, nurses, physicians), which AW and RH are organising in all parts of Switzerland and the neighboring countries, the results of this study will be integrated, and participants will function as multiplicators of the new knowledge.

## Data Availability

No data are available.
